## **1 Background and state of the art**

Alcohol binge drinking, defined as 5 or more drinks for men and 4 or more drinks for women at one time, is the most frequent form of alcohol consumption worldwide, especially in younger people. [1] This drinking pattern is popular and leads to increased mortality and morbidity. Therefore binge drinking is a major public health issue. The behavioural and neurological consequences of binge drinking are well characterized [2-4].

Less is known about the systemic effects on the gut as the first organ in contact with alcohol and on the consequences on inflammation and immune function. Chronic alcohol intake can lead to increased gut permeability, bacterial translocation and alterations in the gut microbiome in animal models. [5-7] Recently bacterial translocation has been shown in healthy volunteers after a single alcohol binge. [8] On immune cells, acute alcohol intake seems to have dichotomous effects. On the one hand alcohol induced liver injury is driven by pro-inflammatory reactions, whereas in the long-term, immunosuppressive and anti-inflammatory effects have been described. [9] These immune effects seem to be driven by endotoxin or other bacterial products via Toll-like receptors that are translocated to the circulation via a defective gut barrier. [10]

## **2 Hypothesis**

We hypothesize that binge drinking impairs gut barrier, increases bacterial translocation and causes inflammation. This leads to an early increase in neutrophil and monocyte function but also an increase in oxidative stress. (see Figure 1).

[figure not shown]

Figure 1: Hypothesis of how alcohol consumption impacts on gut permeability and liver/phagocyte function.

### 3 Preliminary data

In previous research projects we gathered preliminary data that draw a crude picture of the influence that alcohol has on the innate immune system. In 55 abstinent patients with alcohol-induced liver cirrhosis we found that neutrophil function depends on liver synthesis. Patients with compensated cirrhosis (Child-Pugh grade A) showed a significant decrease in phagocytic activity (percentage of phagocytizing neutrophils) but a slight increase in phagocytic capacity (semi quantitative measurement of the number of engulfed bacteria). It is possible that with the increase in inactive cells the remaining functioning cells compensate this loss by increasing their capacity. In decompensated cirrhosis (Child-Pugh grade B/C) this compensation seems to be lost and neutrophil dysfunction becomes apparent.

To clarify the role of liver damage in alcohol induced immune disorder we utilized the Lieber-DeCarli model of alcohol feeding on C57BL/6 mice that exhibit similar damage to the gut barrier and microbiome as humans do but only develop very mild alcoholic liver disease (ALD). We found a significantly increased *ex vivo* clearance capacity of whole blood, a trend to improved neutrophil function, as well as a significantly faster,

more efficient clearance of pathogens from the blood in early stages of experimentally induced sepsis. When the livers of these mice were damaged with 3,5-diethoxycarbonyl-1,4-dihydrocollidine (DDC) before the alcohol feeding period, the before mentioned advantages in *ex vivo* function tests were lost.

We therefore, hypothesize that alcohol by itself has immune activating properties as long as the liver is still functional. However, once the liver has been damaged the effectiveness of the immune system decreases with the degree of liver disease.

[figure not shown]

Fig. 2: A. Phagocytic capacity of neutrophils of 55 patients with alcoholic end stage liver disease (39 Child's A and 16 Child's B or C) compared to 30 healthy controls. Capacity is presented as GMFI weighted by the percentage of active cells, normalized to batch controls. B. Ex vivo clearance capacity of whole blood challenged with *E. coli* of 20 mice on Lieber-DeCarli alcohol or control diet. C. Bacterial load in the blood

stream of 19 mice on Lieber-DeCarli alcohol or control diet 30, 60, 90 minutes and 7 hours after intravenous injection of *E. coli*.

Data presented as mean and SD, \*significant on 5% level (or significant after Bonferroni correction for multiple comparison)

## **4 Study**

This study should test whether one episode of binge drinking in otherwise healthy volunteers causes bacterial translocation and innate immune activation.

### **4.1 Recruitment**

Healthy volunteers will be recruited from the volunteer database of the Clinical Research Center, Medical University Graz

## **5 Endpoints**

Primary endpoint

stool zonulin levels

Secondary endpoints

bacterial translocation

gut permeability

bacterial translocation

inflammation

innate immune function

gut microbiome

## **6 Subject selection**

### **6.1 Inclusion criteria**

- Participant is willing and able to give informed consent for participation in the study.
- Age above 18 years
- Willingness to abstain from alcohol 48h prior to the study visits

## 6.2 Exclusion criteria

- Alcohol abuse
  - Alcohol Use Disorders Identification Test  $\geq 8$  in men or  $\geq 7$  in women
  - or
  - CAGE test  $\geq 2$  (both men and women)
- Elevated liver function test
- Any disease or medication that does not allow concomitant consumption of alcohol
- Women: pregnancy and lactation

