### **Screening visit 1**

Male and female healthy volunteers who accomplish the inclusion criteria and none of the exclusion criteria are eligible for the study and will undergo the following investigation procedures in the screening visit, after signing the informed consent:

- Detailed explanation of the study procedures, including the intake of alcohol under medical supervision
- Check inclusion and exclusion criteria
- Check for demographic data, medical and surgical history and concomitant medication
- Date of birth, gender, smoking status, alcohol consumption
- Body weight and body height
- Vital signs: resting pulse and blood pressure
- Physical examination
- Pregnancy test in women of childbearing age.
- Blood sampling
- Distribution of the material for the gut permeability urine test and stool

sampling

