## 10 Ethical considerations

The study participants are healthy volunteers. They will get a compensation of 100 € for completing all study visits to cover their expenses due to the participation in this study. Binge drinking can potentially be harmful, therefore the dose of alcohol chosen is at the lowest limit to fulfil the definition of binge drinking. Furthermore, several safety measures will be applied: Patients will be monitored until they recover; they are not allowed to drive a car on the day of the study and will therefore receive taxi vouchers or need to use public transport and/or need to be accompanied by an adult friend or family member on their way home.

Participants will not benefit directly for the participation in this study. Participants will benefit indirectly from a detailed assessment of their health status. As a further benefit the Principal Investigator of the study will inform each participant individually on the medical risks of binge drinking at visit 2. Taken together in our view the risks and benefits of the study are balanced.

The protocol, informed consent form and the participant information sheet have been submitted to the Ethics Committee of the Medical University of Graz, Austria.

The Investigator will obtain approval from the Ethics Committee of the Medical University of Graz, Austria for all amendments to the original approved documents.

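### Eligibility limits drinking history only from above, so a healthy adult who has never drunk alcohol can be given the binge drink as a first exposure

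*Protocol*

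**What the plan says.** Protocol section 6.1 has three inclusion criteria: "Participant is willing and able to give informed consent for participation in the study"; "Age above 18 years"; and "Willingness to abstain from alcohol 48h prior to the study visits".

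Section 6.2 has four exclusion bullets:
- alcohol abuse, defined as AUDIT of 8 or more in men or 7 or more in women, or CAGE of 2 or more in either sex;
- "Elevated liver function test";
- "Any disease or medication that does not allow concomitant consumption of alcohol";
- pregnancy or lactation.

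Section 7, Screening visit 1, makes this list sufficient: a volunteer who meets the inclusion criteria and none of the exclusions is eligible. The same visit records "Date of birth, gender, smoking status, alcohol consumption", but no criterion refers to that entry.

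Under Visit 2 in section 7, the alcohol group's drink is scaled to body weight only. Section 10 states: "Binge drinking can potentially be harmful, therefore the dose of alcohol chosen is at the lowest limit". It adds that participants gain no direct benefit.

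**The concern.** The protocol screens for people who drink too much and does not ask whether a person has drunk at all. The exclusion for disease or medication does not close the gap, because it depends on a known incompatibility. Someone who has never taken alcohol has had no opportunity to notice a bad reaction and so has none to report. That criterion therefore protects this person least.

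What is at stake is participant safety. Followed exactly, the plan allows a volunteer's first contact with alcohol to be a deliberate binge-level drink, which the protocol itself regards as potentially harmful and of no direct benefit to the volunteer.

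**Working it through.** The protocol states no figure on this point, so there is none to reproduce. The check takes each criterion in turn for one hypothetical volunteer: a healthy, consenting adult who is not pregnant or lactating and has never drunk.

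| Criterion (Protocol) | Bears on drinking history? | Result for this volunteer |
|---|---|---|
| 6.1 Consent | No | Met |
| 6.1 Age | No | Met |
| 6.1 48 h without alcohol before visits | Short-term only | Met automatically |
| 6.2 AUDIT and CAGE | Upper limit only, no minimum | Not triggered (scores assumed about 0) |
| 6.2 Liver tests | No | Not triggered |
| 6.2 Disease or medication | Known incompatibility only | Not triggered |
| 6.2 Pregnancy, lactation | No | Not triggered |

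Inclusion criteria met: 3 of 3. Exclusion bullets triggered: 0 of 4. Under the Screening visit 1 rule the volunteer is eligible, and nothing in the protocol keeps such a person out of the alcohol group.

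*Exposure.* From section 7, Visit 2: 2 ml/kg × 0.40 = 0.8 ml ethanol per kg. With an assumed ethanol density of 0.789 g/ml, 0.8 × 0.789 = 0.631 g/kg. Over an assumed range of body weights:

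| Body weight (assumed) | Vodka | Ethanol, volume | Ethanol, mass |
|---|---|---|---|
| 50 kg | 100 ml | 40 ml | 31.6 g |
| 70 kg | 140 ml | 56 ml | 44.2 g |
| 90 kg | 180 ml | 72 ml | 56.8 g |

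These amounts are the same for every alcohol-group participant of that weight. They describe what a first exposure would consist of; they do not measure an extra risk to never-drinkers.

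*Safeguards in order of time.* Before the drink there are the consent discussion, the physical examination, the blood and pregnancy tests and the breath test. None of these establishes whether the person has taken alcohol before without harm. After the drink there are monitoring until the breath test is below 0.5 ‰, no driving, and arranged transport home. These apply to never-drinkers as to anyone else in the alcohol group.

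**The case against.** The strongest reply is that this is a choice of population and not an error. Section 4 speaks of otherwise healthy volunteers and section 3 of what alcohol does by itself; a healthy non-drinker fits both. Nothing in the protocol says that participants are drinkers. Volunteers consent after a detailed explanation that includes the alcohol intake, and are told again at Visit 2, so few abstainers may come forward. This stands to the extent that the protocol does not contradict itself here and gives no abstainer rate. It does not remove the gap, because consent informs a volunteer without establishing tolerance, and the eligibility rule still admits this person.

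Three stronger readings are tempting, and the protocol does not support them.
- A reader might infer that never-drinkers would distort the results. No section says that they respond differently on zonulin, translocation or neutrophil function. Section 1 in fact names chronic intake, in animal models, as a cause of altered gut permeability and microbiome, so prior drinking is itself a source of variation.
- A reader might take one person in an alcohol group of 16 as a measure of the effect. That is the share of any participant, whatever the drinking history.
- A reader might infer that the section 10 safeguards leave this person unprotected. They do not: monitoring, the driving ban and transport cover everyone in the alcohol group after the drink.

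Nor is it right that drinking plays no part in eligibility, since AUDIT and CAGE do decide it, but only at the upper end.

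**Conclusion.** The point holds as a safety gap in the eligibility criteria. A healthy adult who has never drunk passes all seven criteria and may be given the binge drink as a first exposure, and no safeguard directed at that situation acts before the drink.

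It rests on one assumption: that a never-drinker scores about 0 on both questionnaires, and in any case below the cut-offs. The protocol does not print AUDIT or CAGE, so this cannot be confirmed from it. How many never-drinkers would enrol cannot be estimated, and no claim is made about the size of any added risk or about bias in the endpoints. The change should be made because the exposure is deliberate, has no direct benefit, and the remedy is cheap. Eligibility is protocol content, so the gap cannot be left to a statistical analysis plan.

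**What to change.** Add one criterion to section 6: the volunteer has previously used, or currently uses, alcohol without adverse reaction. Judge it from the alcohol consumption history already taken at Screening visit 1, and have the investigator set and record the threshold before recruitment. Apply it to all groups, not only the alcohol group, so that they are selected in the same way. If the sponsor does intend to admit people who have never drunk, the protocol should say so and justify it.

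The cost is one line in section 6 and one field on the screening form. A few abstaining volunteers could not take part, and the findings would apply to people who drink. No dose, endpoint or analysis changes.

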## 7 Visit Schedule

Volunteers will undergo 1 screening visit and 2 study visits.

The screening visit duration is approximately 1 hour, the first study visits will last at least 5 hours with an optional observation/recovery period thereafter until the alcohol breath test is below 0.5 ‰. On the next day patients will have to perform the gut permeability test at home and will deliver the urine sample together with a stool sample and a questionnaire to the trial centre.

### Table 1

#### Schedule of assessments

| Visit no.                                                                                                         | 1 (Screening)               | 2 | 3                  |
|-------------------------------------------------------------------------------------------------------------------|-----------------------------|---|--------------------|
| Timing                                                                                                     | 0-28 days prior to visit 1a |   | 24h after visit 1a |
| Inclusion / exclusion criteria                                                                                    | X                           |   |                    |
| Demographics/relevant medical history/current medical conditions                                                  | X                           | X | X                  |
| Physical examination                                                                                              | X                           | X |                    |
| Standard laboratory tests                                                                                         | X                           | X |                    |
| Lactulose/Mannitol/Sucrose Test                                                                                   | X                           |   | X                  |
| pregnancy test (in women of childbearing age)                                                                     | X                           | X |                    |
| Blood sampling for gut permeability, bacterial translocation, oxidative stress and innate immune function (50 ml) | X                           | X |                    |
| Stool sampling                                                                                                    | X                           |   | X                  |
| Dosage administration, adverse events, Concomitant medications/therapies                                          | Ongoing data capture        |   |                    |

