## **Visit 3**

24h after visit 1 they patients will have to perform the gut permeability urine test for 5h at home, collect a stool sample and fill in the self-administered hangover questionnaire and will have to bring the urine sample, the stool sample and the questionnaire to the trial site.

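### The baseline stool for the primary endpoint has no fixed collection date, may lie weeks before the drink, and falls outside the literal 48-hour alcohol-free rule

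*Protocol*

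**What the plan says.** Section 5 names the primary endpoint as "stool zonulin levels", without a time point. Section 8.2.4 analyses continuous variables over time by ANOVA or Friedman tests, so a pre-drink value enters the main comparison.

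In Table 1 (Section 7), the row "Stool sampling" is marked at Visits 1 and 3 and not at Visit 2. The lactulose/mannitol/sucrose test has the same pattern. Visit 1, the screening visit, is timed "0-28 days prior to visit 1a" and Visit 3 "24h after visit 1a".

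The text for the screening visit lists "Distribution of the material for the gut permeability urine test and stool" sampling, with no collection or return step. The Visit 2 text mentions neither stool nor urine. The Visit 3 text has volunteers "collect a stool sample and fill in the self-administered hangover questionnaire" and bring the samples to the site.

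The abstinence condition in Section 6.1 reads "Willingness to abstain from alcohol 48h prior to the study visits". Section 7 opens with "Volunteers will undergo 1 screening visit and 2 study visits".

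**The concern.** The primary result rests on two stool samples per volunteer, and the date of the first is not pinned down. It may be up to four weeks old at the time of the drink, and the rule meant to keep alcohol out of the measurements does not clearly reach it.

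Two things are at stake. The first is precision: diet, medication and microbiome variation over a long gap enter the difference between the samples. The second is dilution: Section 2 hypothesises that a binge impairs the gut barrier. If so, a volunteer's own drinking shortly before the baseline sample shifts that sample in the direction under study and shrinks the measured change.

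The blood markers do not share the problem, because the Visit 2 text takes a blood sample before the drink. A statistical analysis plan cannot repair the stool timing once the samples have been collected.

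**Working it through.** **The passages side by side**

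1. *Anchor.* The visits are numbered 1, 2 and 3, and visit 1a is defined nowhere. Table 1 times Visit 3 at 24 hours after visit 1a; the Visit 3 text counts 24 hours from visit 1, which is screening. The schedule makes sense only if both mean Visit 2. That is an assumption, and it is used below.
2. *Collection.* Section 7 gives the screening visit about 1 hour. The sugar test in Section 8.2.1 needs an overnight fast and 5 hours of urine. With a kit first handed out at screening, the Visit 1 mark for this test cannot be completed at that visit. The samples must come later, on a date that no section gives.
3. *Return.* The only hand-in described, in the opening of Section 7 and in the Visit 3 text, is for the samples taken after the drink.
4. *Abstinence.* Section 6.1 refers to study visits, and Section 7 counts two of these in addition to screening. Read literally, the rule covers Visits 2 and 3. A baseline stool taken in the 48 hours before Visit 2 would be alcohol-free only incidentally, and an earlier one need not be.
5. *A related conflict.* Visit 3 is a study visit 24 hours after the drink, so the alcohol group cannot meet a 48-hour condition before it as worded.

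**Illustration of the noise**

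The protocol gives no SD, effect size, power or correlation, so there is no power calculation to reproduce. Its only relevant figure adds up: 16 + 30 = 46 (Section 8.1). Assumed inputs are the baseline-to-follow-up correlation ρ, two-sided 5% significance, 80% power (1.960 + 0.842 = 2.802) and, for the between-group column, all 30 controls pooled. Everything is in units of the single-measurement SD, by normal approximation.

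- SD of change = √(2(1 − ρ))
- Detectable change within the alcohol group = 2.802 × SD of change × √(1/16)
- Detectable difference between groups = 2.802 × SD of change × √(1/16 + 1/30)

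| ρ (assumed) | SD of change | Within alcohol group (n = 16) | Between groups (16 v 30) |
|---|---|---|---|
| 0.9 | 0.45 | 0.31 | 0.39 |
| 0.8 | 0.63 | 0.44 | 0.55 |
| 0.7 | 0.77 | 0.54 | 0.67 |
| 0.5 | 1.00 | 0.70 | 0.87 |
| 0.3 | 1.18 | 0.83 | 1.03 |

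A longer gap would be expected to move a study down this table. How far is not known from the documents.

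**Illustration of the dilution**

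Suppose k of the 16 baselines in the alcohol group already carried the full effect of recent drinking. The expected mean change is then (1 − k/16) of the true one: 94% for k = 1, 88% for k = 2 and 75% for k = 4. The values of k are assumed. This is an upper case, since a partial effect dilutes less.

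**The case against.** Taking a baseline at screening is a common choice, and this is a pilot meant to gauge the size of an effect, with no power claim to break. That stands, and it limits the severity.

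The strict reading of study visits can be disputed. Section 10 pays volunteers for completing all study visits, which could well include screening, and the strict reading produces a condition that cannot be met at Visit 3. Section 6.2 also excludes volunteers above the AUDIT or CAGE thresholds, and alcohol consumption is recorded at screening. The fair statement is that the rule, as worded, does not secure an alcohol-free baseline; it does not follow that baselines will be contaminated. The exclusions remove problem drinkers but leave ordinary drinkers eligible.

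A reader might infer that the protocol allows the baseline to be taken after the drink, because a 0-day interval is permitted, the kit is only handed out at screening, and no return step is given. The documents do not support that. Table 1 schedules the sample at a visit before the reference visit; what is missing is a return step, and nothing permits a post-drink sample.

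A reader might also infer that the long window biases the comparison of alcohol with control. It does not by itself, because the same window applies to every group. The dilution operates on the within-group change, and on the between-group contrast only if timing or prior drinking differs by group. No such difference is shown.

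Finally, placing everything close to Visit 2 has a drawback of its own: two sugar loads a few days apart could carry over. That stands, and the fix treats the sugar test separately from the stool.

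**Conclusion.** The concern holds as a defect of timing and wording that should be fixed. The protocol leaves the collection and return of the primary-endpoint baseline undated, ties its window to an undefined visit, and does not literally bring it under the alcohol-free condition. The consequences are extra noise in the change over time and possible dilution of the within-group effect.

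The size cannot be derived from the documents. Under assumed correlations of 0.9 down to 0.3, the SD of change runs from 0.45 to 1.18 and the detectable within-group change from 0.31 to 0.83, both in single-measurement SDs. These figures show that the choice can matter in a group of 16; they do not estimate the loss in this trial. The conclusion assumes that visit 1a means Visit 2 and that Sections 6.1 and 7 use the term study visits in the same sense.

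**What to change.** - In Table 1, replace visit 1a with the correct visit number, and reconcile it with the Visit 3 text.
- Move the baseline stool to a short stated window before Visit 2, handed in at Visit 2 before the drink, and record the date and time of collection.
- State that the existing 48-hour alcohol-free condition applies before that collection.
- Give the baseline sugar test its own stated pre-drink date, early enough to avoid carry-over into the Visit 3 test, with a return step.
- Reconcile the 48-hour condition in Section 6.1 with a Visit 3 that falls 24 hours after the drink.

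This is a small amendment to Table 1, the visit texts and one inclusion criterion. It needs no additional kit, assay or visit. The cost is slightly tighter scheduling and an occasional volunteer who produces no stool within the window.
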